#### 7.3.1 Irinotecan Dose Levels

| Current Irinotecan Dose | Dose reduction        |
|-------------------------|-----------------------|
| 180 mg/m    | 150 mg/m  |
| 150 mg/m    | 120 mg/m  |
| 120 mg/m    | 100 mg/m  |
| 100 mg/m    | 85 mg/m   |

Dose reductions beyond 85 mg/m^2 will not be permitted. Once the irinotecan dose is reduced, no dose escalation is permitted.

#### 7.3.2 Hematological toxicities (excluding febrile neutropenia)

Dose reductions will be determined based on blood counts on the day irinotecan should be resumed (unless patient had documentation of grade 4 neutropenia OR had

an episode of febrile neutropenia defined as ANC < 1000 and temperature at least 38.5°C). No dose reductions will be made for anemia.

| Hematological Toxicity
(on day of start of scheduled dose of
irinotecan unless febrile neutropenia
or grade 4 neutropenia) | Action                                                                           | Resumption of therapy                                                                                         |
|-----------------------------------------------------------------------------------------------------------------------------------------------|-----------------------------------------------------------------------------------------|----------------------------------------------------------------------------------------------------------------------|
| ANC 1000-1199
Platelets 75-99 K                                                                                                            | Hold therapy until ANC at least 1200 and Platelets at least 100,000                     | If resolution in 1 week, continue same dose *
If resolution > 1 week, then dose reduce 1 level                    |
| Grade 3 Neutropenia
Grade 2 - 4 Thrombocytopenia                                                                                           | Hold therapy until ANC at least 1200 and Platelets at least 100,000                     | Once resolution to ANC at least 1200 and Platelets at least 100,000, dose reduce 1 level for subsequent treatments * |
| Febrile neutropenia
Grade 4 Neutropenia
(at any time during therapy)                                                                    | Hold therapy until resolution of acute episode and above hematological requirements met | Dose reduce 1 level for subsequent treatments *                                                                      |

\* May consider growth factor support for subsequent treatments.

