## 3 STUDY SPECIFICATIONS

### 3.1 STUDY DESIGN

This is a Phase 1 trial in patients with previously treated stage IV colorectal cancer. The goal is to determine the maximum tolerated dose of ZD6474 with cetuximab and then the maximum tolerated dose of ZD6474, cetuximab and irinotecan.

During the dose finding phase, patients will be enrolled in cohorts of 3. All patients will receive standard doses of cetuximab (400 mg/m^2 loading followed by weekly 250 mg/m^2). Dose levels will be defined as such:

| Dose levels | ZD6474
(daily) | Irinotecan
(q2 wks) | Cetuximab †
(weekly) |
|-------------|-------------------|------------------------|-------------------------|
| 1           | 100 mg            | --                     | 250 mg/m    |
| 2           | 100 mg            | 180 mg/m   | 250 mg/m    |
| 3           | 200 mg            | 180 mg/m   | 250 mg/m    |
| 4           | 300 mg            | 180 mg/m   | 250 mg/m    |

† - after 400 mg/m^2 loading dose

The study will initially enroll into dose level 1. If 0 of 3 patients have a dose limiting toxicity (DLT) then we will advance to dose level 2. If 1 of 3 patients have a DLT, then 3 additional patients will be treated at dose level 1. If 2 patients have a DLT at

dose level 1, the study will close. If <33% of patients have a DLT at dose level 1, we will proceed to dose level 2.

At dose levels 2, we will initiate treatment with irinotecan. Treatment at dose levels 2-4 will begin with 2 weeks of only ZD6474 and Cetuximab. Irinotecan will begin on day 15 (week 3). If 0 of 3 patients have a DLT, we will proceed to the next dose level. If 1 of 3 patients have a DLT, then 3 additional patients will be treated at the same dose level. If 2 patients have a DLT, then the MTD will be current dose level -1 (if on dose level 1, study closes). If < 33% of patients have a DLT, then the study will continue to the next dose level (if at level 4, the MTD for ZD6474 will be considered 300 mg).

Cycles of therapy will be defined as 4 weeks on therapy, even if drugs are held for a portion of that time.

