### 3.2 DOSE LIMITING TOXICITIES

DLTs (defined as within the first 28 days of treatment in dose level 1 and first 35 days in dose levels 2-4) will include: grade IV hematological toxicity > 7 days; fever and neutropenia; grade III diarrhea leading to hospitalization or lasting > 48 hours despite aggressive anti-diarrheal medication; grade IV diarrhea despite aggressive anti-diarrheal medication; grade IV vomiting despite optimal antiemetics; or grade III or higher nonhematological toxicity (excluding nausea, vomiting, diarrhea, or alopecia) lasting > 1 week; grade 4 skin toxicity; grade 3 or greater cardiac toxicities; or death.

If patients in dose levels 2-4 who have a DLT in the first 14 days (prior to initiation of irinotecan), the patient will not be counted towards the DLTs of that cohort and an additional patient will be substituted. For example, if one of the first 3 patients in dose level 2 have a DLT, that patient will not be calculated into the DLT tabulation for ZD6474, cetuximab and irinotecan and an additional patient will be substitute in that spot. If this scenario occurs twice, the study will be held and the study team will reevaluate the ZD6474 / cetuximab toxicities.

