## 5 STUDY PROCEDURES

### 5.1 TREATMENT REGIMEN

Treatment will be administered on an outpatient basis. Expected adverse events and appropriate dose modifications for study drugs are described in Section 6 and 7. No investigational or commercial agents or therapies other than those described below may be administered with the intent to treat the patient's malignancy.

This is a phase I study. Entry into dose levels are described in section 3. Initiation of ZD6474 will occur on the first day of treatment in the clinic or infusion unit. The patient will take the first dose of medication in the presence of the treating clinician or nurse. Thereafter, ZD6474 will be self-administered around the same time daily. If the patient inadvertently does not take the dose at their usual time, or has emesis within 30 minutes of taking ZD6474 tablet, the patient may take that dose any time

within 6 hours of the same day. The daily treatment schedule will be resumed the next day with the patient taking the scheduled dose at their usual time.

Cetuximab will be initiated on the first day of treatment at all dose levels. For the first treatment, ZD6474 should be given first and then at least 30 minutes should elapse prior to start of infusion of cetuximab. For the first treatment, patients will be premedicated with 50 mg IV of diphenhydramine 30-60 minutes prior to receiving 400mg/m^2 IV of Cetuximab over 120 minutes. Subsequently doses will be weekly infusions of 250 mg/m^2 IV over 60 minutes. The infusion rate of cetuximab must never exceed 10 mg/minute (5 mL/min). Premedication with diphenhydramine may be administered prior to subsequent doses, but at the Investigator's discretion, the dose of diphenhydramine (or similar agent) may be reduced.

In dose levels 2-4 and at the MTD (if includes irinotecan), irinotecan will be initiated on day 15 after administration of cetuximab. Irinotecan will be an IV infusion over 90 minutes every other week.

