### Toxicities in Humans

Diarrhea and neutropenia are the major dose-limiting toxicities of irinotecan. Diarrhea can occur in two situations, within the first 24 hours and after 2-4 days. In the former situation, diarrhea may be associated with abdominal cramping and is thought to be mediated by non-competitive inhibition of acetyl cholinesterase activity by irinotecan. This is usually readily treatable with atropine, 0.25-1 mg, intravenously.

When diarrhea occurs late (after 2-4 days), and often after the second or third weekly dose of irinotecan, it can be a potentially serious event. In contrast to early diarrhea, delayed diarrhea appears to be secretory in nature and to result from abnormal intestinal ion transport. Anti-diarrheal agents, such as loperamide, diphenoxylate-atropine (Lomotil®), octreotide, scopolamine and bismuth are typically ineffective once grade IV diarrhea has occurred. The diarrhea usually lasts 5-7 days before resolving. Early recognition of diarrhea and prompt institution of an intensive and prolonged course of loperamide appears to be the most effective approach to this problem. It is recommended that patients take 4mg of loperamide immediately after their first loose bowel movement. Loperamide 2mg should be taken every 2 hours for a total of 12 hours if diarrhea persists. If no further loose bowel movements occur, therapy may be discontinued.

Myelosuppression is manifested primarily as leukopenia and neutropenia. Other toxicities include nausea, vomiting, alopecia and cumulative fatigue or asthenia. Instances of possible drug related hepatic toxicity have occurred, but are rare. Further descriptions are found in the package insert for irinotecan.

Several cases of interstitial pneumonitis have been reported, predominantly in the Japanese literature, with an incidence of 1.3%. Most reports have occurred in patients with primary lung tumors, where it is unclear whether the pulmonary toxicity was attributable to irinotecan, to progression of the underlying malignancy or to a combination effect. Clinically, this is manifested as worsening shortness of breath, fever and a reticulonodular infiltrate on CXR. Corticosteroids may be helpful in treatment. Hence, the exact mechanism by which pulmonary toxicity is mediated is unknown; however, a current belief is that it may represent an idiosyncratic reaction to the drug. No characteristic histologic correlates have been identified.

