## **7 DOSE and SCHEDULE MODIFICATIONS**

This Phase I study is intended to establish the maximum tolerated dose (MTD) of the combination of cetuximab, ZD6474 and irinotecan. DLTs (defined as within the first 28 days of treatment in dose level 1 and first 35 days in dose levels 2-4) will include: grade IV hematological toxicity > 7 days; fever and neutropenia; grade III diarrhea leading to hospitalization or lasting > 48 hours despite aggressive anti-diarrheal medication; grade IV diarrhea despite aggressive anti-diarrheal medication; grade IV vomiting despite optimal antiemetics; or grade III or higher nonhematological toxicity (excluding nausea, vomiting, diarrhea, or alopecia) lasting > 1 week; grade 4 skin toxicity; grade 3 or greater cardiac toxicities; or death. If patients in dose levels 2-4 who have a DLT in the first 14 days (prior to initiation of irinotecan), the patient will not be counted towards the DLTs of that cohort and an additional patient will be substituted. For example, if one of the first 3 patients in dose level 3 have a DLT, that patient will not be calculated into the DLT tabulation for ZD6474, cetuximab and irinotecan and an additional patient will be substituted in that spot. If this scenario occurs twice, the study will be held and the study team will reevaluate the ZD6474 / cetuximab toxicities.

Patients should remain on the assigned doses of therapy throughout the period of assessment of DLTs (first 28 days in dose level 1 and 35 days in dose levels 2-4) unless a DLT is observed or the patient is withdrawn from study for other reasons. The following guidelines for dosing delay and/or dose modifications apply to patients who either experience a DLT during the first 28 days (dose level 1) or 35 days (dose levels 2-4) OR develop treatment-related toxicities after that period of assessment.

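### Section 7.3.2 judges platelets only on the irinotecan dosing day, so a recovered between-dose grade 4 platelet count brings no dose reduction, unlike grade 4 neutropenia (minor)

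*Protocol*

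**What the plan says.** Section 7 fixes when the modification rules operate. During DLT assessment (35 days at dose levels 2-4, the only levels with irinotecan), "Patients should remain on the assigned doses of therapy throughout the period of assessment of DLTs", unless a DLT occurs or the patient is withdrawn. The rules then cover patients who have had a DLT in that window and those who "develop treatment-related toxicities after that period of assessment".

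Within that scope, section 7.3.2 states its general principle and its exceptions together: "Dose reductions will be determined based on blood counts on the day irinotecan should be resumed (unless patient had documentation of grade 4 neutropenia", followed by febrile neutropenia as the second exception. The table header repeats these two exceptions. The last row, for febrile and grade 4 neutropenia, is marked "at any time during therapy" and leads to a one-level reduction. Grade 2-4 thrombocytopenia stands in the row above, under the dosing-day header and without that marking. Anemia is expressly excluded as a reason to reduce.

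The DLT definition in section 3.2 does not separate cell lines: it lists "grade IV hematological toxicity > 7 days".

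**The concern.** Platelets and neutrophils are handled differently for the same severity between doses. A patient with a documented grade 4 platelet count that has recovered by the next dosing day meets no reducing row of the table and is re-treated at the same dose. A patient with grade 4 neutropenia and equally recovered counts loses one level. The same table also lowers the dose for a milder platelet count, grade 2, if it is found on the dosing day.

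What is at stake is the safety of one patient's next irinotecan dose. As written, the rule reaches even a platelet DLT under section 3.2 that recovers in time.

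**Working it through.** The plan gives no figure to reproduce here. The check traces the 7.3.2 table by hand and then sizes the result.

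**Inputs**
- Scope of the rules and the 35-day window: section 7.
- Dosing-day test, its exceptions and the count thresholds: section 7.3.2.
- Irinotecan schedule: it starts on day 15 (section 3.1), and "Irinotecan will be an IV infusion over 90 minutes every other week" (section 5.1).
- Dose steps (180 to 150 mg/m2) and no re-escalation: section 7.3.1.
- Scheduled blood counts: section 10.
- Cohort sizes: up to 6 per level (section 3.1), plus 10 at the MTD (section 13).

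**Trace where the section 7 rules apply**

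| Event | Dosing-day state | Result under 7.3.2 |
|---|---|---|
| Grade 4 platelets between doses | Platelets at least 100,000, ANC at least 1200 | No row met: same dose |
| Grade 4 platelets between doses | Platelets 75-99 K, resolved within 1 week | Hold, then same dose |
| Platelets just under 75 K on the dosing day (grade 2) | Not recovered | Hold, then reduce one level |
| Grade 4 neutropenia between doses | Fully recovered | Reduce one level |
| Platelet DLT (grade 4 for more than 7 days) | Recovered as in row 1 or 2 | Same dose |

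Row 1 and row 4 differ only in the cell line.

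**Does other text close the gap?**
- Section 7.3.5 reduces for grade 3/4 toxicity, but only for other toxicities. Section 7.3 lists the platelet count separately from other irinotecan-related toxicity, and 7.3.2 has its own platelet rule.
- Section 7.1.6 changes ZD6474, not irinotecan.
- The resumption thresholds in section 7.3 are already met by a recovered count.

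None of them supplies a reduction.

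**Timing**
- Irinotecan days: 15; 15 + 14 = 29; 29 + 14 = 43.
- Days 15 and 29 fall inside the 35-day window. Without a DLT, toxicity arising on days 36-42 first bears on the day-43 dose.
- A platelet DLT takes more than 7 of the 14 days between doses, which leaves less than 14 - 7 = 7 days for onset and recovery. Reaching 75-99 K by the dosing day and resolving within the following week is enough for the same dose. The case is possible but tight.

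**Detection**
- Scheduled CBCs fall in cycle 1 week 3 and then in weeks 1 and 3, which are the irinotecan weeks. A between-dose count is therefore unscheduled. The same holds for between-dose grade 4 neutropenia, which the plan does cover.

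**Size**
- Most patients who could receive irinotecan by design, apart from replacements: 3 levels x 6 + 10 = 28, of the overall maximum 4 x 6 + 10 = 34.
- First event, no reduction against reduction: 180/150 = 1.20, so 20% higher.
- Cost of a reduction: (180 - 150)/180 = 30/180 = 16.7%.

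**The case against.** The strongest reply is that this is a deliberate and coherent rule.

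- The same two exceptions appear in the lead-in, the header and the last row, and nothing contradicts them. This stands. A reader might infer that 7.3.2 is self-contradictory, but it is not.
- Section 6.2 says "Diarrhea and neutropenia are the major dose-limiting toxicities of irinotecan", describes myelosuppression mainly in terms of white cells, and does not name thrombocytopenia among irinotecan's toxicities. That partly explains an any-time rule for neutrophils alone.
- A reader might argue that the omission must be an oversight because, on the dosing day, reduction starts at grade 2 for platelets but at grade 3 for neutrophils. This mixes two questions: recovery in time for the next dose, and depth of the nadir. Grade 3 neutropenia between doses that recovers does not reduce the dose either. Dosing-day recovery is the table's general principle, with a narrow exception for neutropenia.
- Section 7 calls its rules guidelines, and after the window nothing forbids a clinician from reducing the dose. That softens the consequence but leaves the written rule as it is.
- Reach is very small. This also stands.

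What survives is narrower. Section 3.2 counts prolonged grade IV hematological toxicity as dose-limiting whatever the cell line, yet following 7.3.2 as written re-treats at the same dose after documented grade 4 thrombocytopenia, including a platelet DLT that has recovered.

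**Conclusion.** The point holds as a minor, inexpensive safety improvement. Where the section 7 rules apply, a documented between-dose grade 4 platelet count that recovers as described leads to the same irinotecan dose, while grade 4 neutropenia at any time leads to one level less. For a first event from 180 mg/m2, the next dose is 20% higher than it would be with the reduction.

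This rests on reading the platelet row as governed by the dosing-day header, and on an unscheduled count having been taken. No frequency is claimed, since the protocol gives no platelet rate for this regimen.

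Two stronger inferences are not supported. DLT counts, the MTD and the analyses do not change, because DLTs are defined in section 3.2 independently of 7.3.2. Nor should a non-DLT platelet nadir inside the window have lowered the day-29 dose, because section 7 keeps assigned doses until the window closes. The front matter records closure to new accrual, so in this trial the point can matter only for patients still on treatment.

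**What to change.** Add grade 4 thrombocytopenia in three places in section 7.3.2: the exceptions in the lead-in, the exceptions in the table header, and the last row with its existing any-time marking. Keep that row's present action: hold until counts recover, then reduce one level. Grade 4 platelets found on the dosing day already receive that action, so the rows do not conflict.

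If a scope note is wanted, confine it to the new entry: *For grade 4 thrombocytopenia that is not a DLT, the reduction applies only to events after the DLT assessment period (section 7); hold rules always apply.* A note covering all three events should be avoided. It would change how grade 4 and febrile neutropenia are handled in the window and could be misread as overriding the holds.

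The cost is a few words, with no new tests or visits. The downside is a rare reduction of about 17% (180 to 150 mg/m2) in a patient whose platelets have recovered. It is permanent because section 7.3.1 allows no re-escalation, and the plan already accepts the same cost for grade 4 neutropenia.

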### 7.3.3 Cholinergic reactions

Lacrimation, rhinorrhea, miosis, diaphoresis, hot flashes, flushing, abdominal cramping, diarrhea, or other symptoms of early cholinergic syndrome may occur during or shortly after receiving irinotecan. Atropine, 0.25-1.0 mg IV or SC may be used to treat these symptoms. In patients with troublesome or recurrent symptoms, prophylactic administration of atropine shortly before irinotecan therapy may be considered. Additional antidiarrheal measures may be used at the discretion of the treating physician. Anticholinergics should be used with caution in patients with potential contraindications (e.g., obstructive uropathy, glaucoma, tachycardia, etc.).

### 7.3.4 Late diarrhea (e.g., developing more than 24 hours after irinotecan)

Late diarrhea should be managed with anti-diarrheal medications as judged by treating physician (including loperamide, lomotil, deodorized tincture of opium). Irinotecan must be held until diarrhea resolves to no greater than grade 1. The following dose modifications are based on toxicities experienced during a cycle:

| Diarrhea grade                                   | Action                      | Resumption of therapy                            |
|---------------------------------------------------------|------------------------------------|---------------------------------------------------------|
| Grade 2/3 diarrhea
Not optimal antidiarrheal therapy | Hold until no greater than grade 1 | Resume same dose but optimize anti-diarrheal management |
| Grade 2/3 with optimal antidiarrheal therapy            | Hold until no greater than grade 1 | Resume with 1 level dose reduction                      |
| Grade 4 diarrhea                                        | Hold until no greater than grade 1 | Resume with 1 level dose reduction                      |

### 7.3.4 Nausea/Emesis

Nausea / emesis should be managed with anti-nausea medications as judged by treating physician. Irinotecan must be held until nausea/emesis resolves to no greater than grade 1. The following dose modifications are based on toxicities experienced during a cycle:

| Grade                                                           | Action                      | Resumption of therapy                         |
|------------------------------------------------------------------------|------------------------------------|------------------------------------------------------|
| Grade 2/3 nausea
Grade 2/3 vomiting
Not optimal anti-nausea meds | Hold until no greater than grade 1 | Resume same dose but optimize anti-nausea management |
| Grade 2/3 nausea
Grade 2/3 vomiting with optimal anti-nausea meds   | Hold until no greater than grade 1 | Resume with 1 level dose reduction                   |
| Grade 4 vomiting                                                       | Hold until no greater than grade 1 | Resume with 1 level dose reduction                   |

### 7.3.5 Other toxicities

Other toxicities attributable to irinotecan as deemed by the investigator (except alopecia) should be managed as such

| Grade                         | Action                      | Resumption of therapy       |
|--------------------------------------|------------------------------------|------------------------------------|
| Grade 0,1,2 other toxicity           | Continue irinotecan                | No dose reductions                 |
| Grade 3/4 toxicity (except alopecia) | Hold until no greater than grade 2 | Resume with 1 level dose reduction |

